## Abstract

**Background:**

Treatment of psychotic disorders consists primarily of second generation antipsychotics, which are associated with metabolic side effects such as overweight/obesity, diabetes, and dyslipidemia. Evidence-based clinical practice guidelines recommend timely assessment and management of these conditions; however, research studies show deficits and delays in metabolic monitoring and management for these patients. This protocol article describes the project ‘Monitoring and Management for Metabolic Side Effects of Antipsychotics,’ which is testing an approach to implement recommendations for these practices.

**Methods/Design:**

This project employs a cluster randomized clinical trial design to test effectiveness of an evidence-based quality improvement plus facilitation intervention. Eligible study sites were VA Medical Centers with ≥300 patients started on a new antipsychotic prescription in a six-month period. A total of 12 sites, matched in pairs based on scores on an organizational practice survey, were then randomized within pairs to intervention or control conditions.

Study participants include VA employees involved in metabolic monitoring and management of patients treated with antipsychotics at participating sites. The intervention involves researchers partnering with clinical stakeholders to facilitate tailoring of local implementation strategies to address barriers to metabolic side-effect monitoring and management. The intervention includes a Design Phase (initial site visit and subsequent development of a local implementation plan); Implementation Phase (guided by an experienced external facilitator); and a Sustainability Phase. Evaluation includes developmental, implementation-focused, progress-focused and interpretative formative evaluation components, as well as summative evaluation. Evaluation methods include surveys, qualitative data collection from provider participants, and quantitative data analysis of data for all patients prescribed a new antipsychotic medication at a study site who are due for monitoring or management of metabolic side effects during the study phases. Changes in rates of recommended monitoring and management actions at intervention and control sites will be compared using time series analyses.

**Discussion:**

Improving monitoring for metabolic side effects of antipsychotics, as well as promoting timely evidence-based management when these effects emerge, will lead to improved patient safety and long-term outcomes. This article discusses key strengths and challenges of the study.

**Trial registration:**

NCT01875861

## Background

Psychotic disorders are prevalent, disabling and costly among Veterans receiving healthcare in the U.S. Department of Veterans Affairs (VA) and elsewhere. For example, while 3.4% of VA service users have a diagnosis of schizophrenia, patients with this serious mental illness (SMI) account for 11.7% of VA healthcare costs [1]. In Fiscal Year (FY) 2010, about 242,000 patients with a psychotic disorder diagnosis (*e.g*., schizophrenia, bipolar disorder) were treated in the VA [2]. Over 90% of these patients who are treated with antipsychotic medication are prescribed a second-generation antipsychotic (SGA) medication. Unfortunately, as was recently reinforced by the landmark Clinical Antipsychotic Trials of Intervention Effectiveness (CATIE) study [3], treatment with many SGAs is associated with metabolic side effects such as overweight/obesity, diabetes, and dyslipidemia [4-7]. Failure to properly monitor and manage these side effects can lead to increased risk of mortality due to diabetic ketoacidosis [8] and cardiovascular disease [9]. In addition to these treatment-emergent adverse effects, patients with SMIs such as schizophrenia already have a greater prevalence of obesity (42%) [10,11] and diabetes (13%) [12] than the general population.

### Recommendations for monitoring and management of metabolic side effects

A national conference organized in 2002 by the VA Mental Health Quality Enhancement Research Initiative (MH QUERI) and others developed evidence- and expert consensus-based recommendations for metabolic side-effect monitoring [13]. Subsequently, similar recommendations were developed by a joint panel of the American Diabetes Association (ADA) and the American Psychiatric Association (APA) [14]. Monitoring recommendations from both of these sources were incorporated in the 2004 VA/Department of Defense (DoD) Psychoses Guidelines update [15], and relevant evidence-based management recommendations are contained in VA clinical practice guidelines (CPG) for obesity [16], diabetes [17] and dyslipidemia [18]. Briefly, monitoring of weight or body mass index (BMI), fasting plasma glucose (FPG), and fasting plasma lipids is recommended when a patient is started on a new antipsychotic medication, with monthly follow-up monitoring of weight/BMI, and FPG and lipid profile monitoring at three to four months and annually thereafter [13,14]. In addition, the ADA/APA panel suggested using SGAs with lower propensity for weight gain. Ziprasidone and aripiprazole are least likely to cause weight gain, while olanzapine and clozapine are the most likely [14]. Another recommendation from the CPG for Screening and Management of Overweight and Obesity [16] provides strong evidence-based recommendations that overweight or obese patients be offered weight loss interventions that combine dietary therapy, increased physical activity, and behavioral modification strategies. Implementation of the overweight/obesity CPG is specifically supported by the ‘MOVE!’ Weight Management Program for Veterans, a national VA-designed program to help Veterans lose weight, keep it off, and improve their health [19].

### Existing VA practice, patterns and outcomes

Both VA [7,20-22] and non-VA [23-25] studies have found low rates of metabolic monitoring among patients treated with antipsychotics. Surprisingly, there are no published studies that examine the rates for management of metabolic side-effects that develop in the context of newly-initiated antipsychotic treatment or antipsychotic medication changes, although substantial improvement is likely needed in these practices as well. In a recent study of 32 VA facilities, metabolic monitoring frequency was greater at baseline (*i.e*., within 30 days before to 30 days after the new prescription date) than at initial follow-up (*i.e*., 60 to 120 days after prescription date), although at both times monitoring was low. For example, baseline monitoring rates compared to follow-up rates were 67% versus 49% for weight, 46% versus 27% for glucose or hemoglobin A1c, and 32% versus 16% for LDL [20].

### Preliminary studies and related developments

A previous project, ‘A Study of Strategies for Improving Schizophrenia Treatment (ASSIST),’ compared the effectiveness of two strategies aimed at improving medication management for schizophrenia – a team-based quality improvement strategy (Team QI) and a strategy involving a single clinical opinion leader (OL) at six sites in two Veterans Integrated Service Networks (VISNs). Both strategies were aided by an evidence-based QI (EBQI) approach and external facilitation (EBQI/F). While both Team QI and OL strategies resulted in improvements in metabolic monitoring rates at the time of a new antipsychotic prescription, neither strategy was clearly superior to the other. The study suggested that: designating a provider or clinic to ensure completion of monitoring, and implementing a computer routine that queried the VA electronic medical record to identify patients due for monitoring were effective QI components.

Subsequently, in December 2007, the VA Office of Inspector General (OIG) reported on their examination of metabolic monitoring and management for patients on atypical antipsychotics for ≥90 days [26]. Rates of monitoring described in the OIG report were higher than in other studies (*e.g*., 88% of patients had an FPG test in the past year) because of longer observation periods than in other studies. For obese or overweight patients (82% of the sample), 21% did not have any record of a weight management intervention. Of the 17% of patients with elevated glucose in the past three years, only 49% had documented management. A limitation of this study was that it looked at any metabolic management within the past year, rather than examining timely intervention for abnormal monitoring results. The OIG report and VA research clearly demonstrate the need for more timely guideline-concordant management of antipsychotics’ metabolic side effects.

Also in 2007, MH QUERI and the South Central Mental Illness Research, Education and Clinical Center (MIRECC) sponsored an expert panel meeting to further operationalize metabolic monitoring recommendations and consider applicability of the other VA/DoD CPG recommendations for management of metabolic side effects. Panel discussions informed a subsequent task force, the Atypical Antipsychotic Workgroup, formed by VA Mental Health Services in 2008. Both groups, after review of existing guidelines and relevant scientific literature, noted the importance of broad dissemination of evidence-based and expert consensus-based recommendations for monitoring and managing antipsychotic side effects.

### MIRECC initiative on antipsychotic monitoring improvement project

Following the Atypical Antipsychotic Workgroup report, Mental Health Services funded the MIRECC Initiative on Antipsychotic Monitoring Improvement (MIAMI) Project to broadly disseminate metabolic monitoring and management recommendations along with promising tools, strategies, and technical assistance to support relevant quality improvement efforts. The MIAMI Project team included clinical and research experts in psychopharmacology, SMI, and implementation science, who further operationalized metabolic monitoring and management recommendations. The MIAMI Project included:

1. A national training meeting (May 2010) attended by approximately 100 providers and clinical managers;

2. The MIAMI Project Technical Assistance Center (TAC) to assist providers and clinical managers in developing quality improvement efforts and to provide additional information on MIAMI Project tools/resources; and

3. A VA intranet website (http://vaww.mirecc.va.gov/miamiproject), with links to relevant clinical practice guidelines, educational resources, and weight management resources.

Available MIAMI Project tools include examples of computerized clinical reminders, a poster summarizing monitoring and management recommendations, an automated computer routine to identify patients due for initial metabolic monitoring, and a psychoeducational weight management program [27,28].

The protocol presented in this article is for the project, ‘Monitoring and Management for Metabolic Side Effects of Antipsychotics,’ which is testing an EBQI/F implementation intervention to enhance uptake of evidence-based tools and strategies to improve monitoring and management of metabolic side effects of antipsychotics concurrently with the MIAMI Project’s VA national implementation effort. We anticipate that the national implementation effort will improve care overall, although the improvement is likely to be variable as there are a substantial number of facilities that have fewer resources and more difficulty mounting QI efforts, and that do not have formal coordination between mental health and primary care clinics for managing metabolic side effects in patients taking antipsychotics. Therefore, we are studying the national implementation effort at multiple sites, using a cluster randomized design, assessing organizational challenges at these sites, and testing an intervention that includes EBQI [29,30] and external facilitation [31,32] strategies to customize, adapt and enhance the impact of local strategies for implementation of the national QI initiative. We stratified sites based on scores on an organizational practice survey, and randomized at the site level, recognizing that organizational context is likely to be a strong predictor of implementation success. Results will inform ongoing VA implementation of tools and strategies to improve metabolic monitoring and management, as well as future implementation research to improve care at all VA facilities, not just sites that have adequate resources and QI infrastructure.

### Study objectives

1. To test the effect of an EBQI/F intervention as an augmentation to the national implementation initiative on monitoring of metabolic side effects of antipsychotics in sites likely to encounter greater challenges to implementation (see Site Selection below).

2. To test the effect of the EBQI/F intervention as an augmentation to the national implementation initiative on management of metabolic side effects of antipsychotics in sites likely to encounter greater challenges to implementation.

3. To assess the direct costs of the EBQI/F intervention, and explore potential variations in costs of the EBQI/F intervention in sites with lower versus higher levels of organizational challenges.

## Methods

This study employs a cluster randomized clinical trial design, with matched pairs of VA facilities defined as the clusters, to test the effectiveness of an EBQI plus facilitation (EBQI/F) intervention combined with the ongoing national quality improvement initiative (MIAMI Project) at six sites (intervention sites) compared to six matched comparison sites exposed to the national quality improvement initiative alone (control sites). The extent to which metabolic monitoring and management recommendations are followed will be examined at the intervention sites over three six-month intervals: the Pre-implementation Phase, defined as the six-month period prior to the initial EBQI site visit at the intervention sites; the Implementation Phase, which includes active external facilitation (EBQI/F); and the Sustainability Phase, during which the research team continues to evaluate the extent of metabolic monitoring and management, but external facilitation is not provided (see Figure 1). Each control site will be examined over the same three six-month periods as the matched intervention site. During the initial site visit, and for a variable period of time following the visit (the EBQI Design Phase), each intervention site’s EBQI participants will work with the facilitator to develop a local implementation plan. If preliminary results indicate that the EBQI/F intervention is successful, control sites will be offered the EBQI/F intervention in a Crossover Phase at the conclusion of the study.

**Figure 1 F1:**
[figure not shown]
Study timeline of implementation/evaluation phases for each matched pair of sites.

### Site selection

Our systematic site selection method used data extracted from national VA databases and determined that 99 VA Medical Centers had 300 or more patients with a new antipsychotic prescription in the first six months of FY08. Next, to identify sites likely to perform relatively poorly in management of metabolic side effects, we determined the proportion of patients at each site who received a primary or secondary stop code for an encounter with the VA’s ‘MOVE!’ Weight Management Program in the six months following the new antipsychotic prescription. We used the referral to the ‘MOVE!’ Program as an indicator of provider attention to adverse medication side effects, since weight gain is a common side effect of antipsychotic use. The median proportion of patient encounters with the ‘MOVE!’ Program per site was 1.2% and the range was 0% to 4.3%. These results are similar to a previous finding that only 2% of overweight patients with schizophrenia receive recommended medication changes [33].

We then excluded sites not involved in research, using the Office of Research & Development’s directory of research programs. From those sites located within the contiguous 48 states with active research programs, we contacted the mental health clinical manager at the 24 sites with the lowest proportions of ‘MOVE!’ Program utilization (range 0% to 0.66%). Three of the 24 sites were excluded because of an active or planned research project to study metabolic monitoring and/or management. Two sites were excluded because they already had primary care clinicians integrated into mental health clinics. Two sites declined to participate, and leaders at three other sites did not respond to repeated requests for participation in the project. Leaders at the remaining 14 sites attended conference calls with the study PI to obtain further information, and each agreed to have their site included in the final site selection pool. Each completed a brief survey, adapted from a VA Clinical Practice Organizational Survey that included questions on provider stress and ability to pursue practice change [34,35]. Survey scores ranged from 16.1 to 74.2 on a 100-point scale, with higher scores indicating higher levels of stress and lower capacity to pursue practice change. Sites were ranked according to survey scores. The 12 sites with the highest scores were invited to participate in the study, and all accepted. We used the ranked list of sites to identify matched pairs with comparable survey scores, and then randomly selected one site from each pair to receive the intervention, using a random number generator tool available at http://www.random.org. The mean survey score of the intervention sites was 48.9 compared to 51.1 for the control sites. Shortly after this matching, two of the sites withdrew from study participation; however, fortunately, the remaining two sites that had not initially been selected for study inclusion agreed to participate. Both of these sites had low scores on the Clinical Practice Organizational Survey, and thus did not affect the distribution of intervention and control sites on this inclusionary variable. Soon after this change, another site withdrew from the study; however, this occurred at about the same time that one of the previous sites that had earlier declined participation was now willing to participate. Both of these sites had been randomized to the intervention arm, and so the newly available site replaced the withdrawn site, resulting again in 12 sites participating in the study: 6 intervention sites and 6 control sites.

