### Site selection

The research team employed a systematic site selection process rather than identifying a convenience sample of frequently-utilized study sites. The selected sites thus are more likely to be representative of the diversity of VA facilities, with respect to size, extent of academic affiliation, resources available to pursue quality improvement efforts, and scores on the organizational practice survey than would have been the case if a convenience sample of sites was selected. Systematic site selection ensures that study findings will be broadly generalizable to the majority of VA facilities, and enables the research team to identify unique site implementation barriers and facilitators.

Despite the potential benefits of this site selection method, it also has caused challenges. While we pursued IRB approval, our contacts at 3 of the 12 initially selected sites indicated that the site would be unable to participate in the study (*e.g*., because the leader who originally agreed was no longer in the same position). This experience suggests that a disadvantage of the systematic site selection process is that there may be more attrition than when convenience sampling is employed; perhaps investigators could develop retention strategies to maintain site leaders’ interest in the study and encourage them to overcome participation barriers during the sometimes lengthy waiting period between grant submission and final funding. A study team could include back-up sites in the site selection approach, although it may not be possible to activate a replacement site once the study has started. Finally, investigators should recognize that a site that withdraws after the start of implementation activities should still be included in an ‘intent-to-implement’ analysis.

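### Three of the 12 randomised sites left after the draw and two of their replacements were never in it, with no random assignment reported, so the final arms are not the arms as randomised

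*Protocol article*

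**What the plan says.** The Abstract describes 12 sites, matched in pairs, that "were then randomized within pairs to intervention or control conditions". The Site selection section under Methods gives the sequence of events:

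- Fourteen sites formed the pool. "The 12 sites with the highest scores were invited to participate in the study, and all accepted". The investigators ranked and paired them, and "then randomly selected one site from each pair to receive the intervention". Mean survey scores of 48.9 (intervention) and 51.1 (control) are given at this point, before any withdrawal is mentioned.
- "Shortly after this matching, two of the sites withdrew from study participation". In their place, "the remaining two sites that had not initially been selected for study inclusion agreed to participate". The text then says "Both of these sites had low scores on the Clinical Practice Organizational Survey" and concludes that the distribution of arms on this variable was not affected. It gives neither the arms of the two leavers nor the way the two reserves were assigned.
- A further site withdrew at about the time that a site which had previously turned the study down became willing. The reason given for the swap is "Both of these sites had been randomized to the intervention arm, and so the newly available site replaced the withdrawn site".

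The Site selection part of the Discussion confirms that 3 of the 12 initially selected sites were lost, while IRB approval was being sought. It also advises that "a site that withdraws after the start of implementation activities should still be included in an" intent-to-implement analysis.

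**The concern.** Randomisation protects the comparison only for the sites that were in the draw, analysed in the arms they drew. Here a quarter of the clusters changed after the draw. With six sites per arm, one changed site is a sixth of that arm's average. The Background says the investigators expect organisational context to predict implementation success strongly, and the two reserves differ from the other sites on exactly the survey used to capture it. If the final 6 versus 6 is described simply as randomised within pairs, readers will give the result more causal weight than the allocation supports. They will also take the reported score balance to describe the sites actually studied.

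**Working it through.** **1. Site counts (Methods, Site selection).** Pool: 24 − 3 − 2 − 2 − 3 = 14. Randomised: 12. After the swaps: 12 − 2 + 2 − 1 + 1 = 12. The article's final total of 12 (6 and 6) reproduces. Lost after the draw: 3/12 = 25%.

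**2. Who the third replacement can have been.** The article says that it had turned the study down before and also that it had been randomised to intervention. All 12 invited sites accepted, and sites that declined at the contact stage never entered the pool.

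- *Reading A: it was one of the first two withdrawals, returning.* Both statements can then be true. It had left an intervention slot at the first swap. The third swap was intervention for intervention and ended at 6/6, so the split was already 6/6 after the first swap. The vacated intervention slot had therefore been filled, and only the two reserves were available to fill it. The Discussion counts all three losses among the initially selected sites, so that reserve was not the third site to leave. Result: 10 drawn sites and 2 undrawn (2/12 = 17%), with at least one undrawn reserve in the intervention arm.
- *Reading B: it declined before the pool was formed.* It was then never randomised, and the stated reason for the swap is wrong. Result: 9 drawn sites and 3 undrawn (25%), one of them in the intervention arm by direct placement.

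**3. Pairs.** Three lost sites belong to at least 2 and at most 3 pairs, so 4 or 3 of the 6 original pairs are intact.

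**4. Survey scores.** The range over the 14 sites is 16.1 to 74.2. The 12 highest were taken, so the reserves are the two lowest and one of them scored 16.1. Replacing a site that scored x with the 16.1 site moves that arm's mean by (16.1 − x)/6. The leavers' scores are not given, so x is assumed:

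| Score of site replaced (assumed) | Shift in arm mean |
|---|---|
| 30 | −2.3 |
| 50 (the mean of the 12: (48.9 + 51.1)/2) | −5.7 |
| 74.2 | −9.7 |

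The published gap is 51.1 − 48.9 = 2.2 points. The gap could stay small if one reserve joined each arm in place of similar leavers, but the article does not say so, and both means would then fall.

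**5. Table 3, reproduced first.** Slope variance per site = v_b + the AR(1) variance of a slope over 6 monthly points. In the expected scenario this is 5.3 + 7.31 = 12.61. SE of the difference between arms = √(2 × 12.61/6) = 2.05. At 80% power, two-sided 0.05 and 20 df (the article gives no df; this value fitted best), the multiplier is 2.945. The detectable difference is 6.04 against the printed 6.1. The other two scenarios give 5.21 (printed 5.3) and 7.17 (printed 7.2).

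**6. Size of a possible shift.** Assume that an entering site's slope exceeds that of the site it replaced by one between-site SD: √5.3 = 2.30 points/month. The contrast moves by 2.30/6 = 0.38 points/month per site, or 0.38/6.1 = 6% of the detectable difference. Treating all three entrants this way, the net depends on their arms:

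- all three in intervention: 3 × 0.38 = +1.15;
- Reading B with both reserves in control: (1 − 2) × 0.38 = −0.38.

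The signs reverse if entering sites do worse than those they replaced.

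**7. What a restricted analysis can show.** Scaling 6.04 by √(6/n) gives 7.4 for 4 intact pairs and 8.5 for 3, with df held at 20, so both are understated. The smallest two-sided permutation p-value, 2/2^n, is 0.125 or 0.25, against 2/64 = 0.031 for six pairs.

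**The case against.** The third swap, taken as written, is the mildest of the three: the incoming site is said to have drawn intervention already, so it kept its arm. That stands, and the point rests mainly on the two reserves. For them the article is silent on assignment, and the full protocol may describe a draw. If the first two leavers came from opposite arms, the reserves could have been randomised between the two slots. The most that can be said is that no draw is reported.

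Three stronger readings are tempting and are not supported:

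- *Unwilling intervention sites were exchanged for willing ones, which favours EBQI/F.* The losses came during IRB approval, before any site visit. The one example reason is a leader changing post. Whether sites knew their arm is not stated. The reserves had already agreed to be in the pool, like the other 12.
- *The intent-to-implement wording leaves out sites lost in the Design Phase.* The sentence is general advice in the Discussion and not this trial's analysis-set rule. Table 2 counts design meetings among implementation activities, so such a loss may well be covered.
- *Type I error is inflated.* Values of about 5.4%, 6.6% and 8.7% follow for one, two or three entering sites only if each has the assumed one-SD advantage and all are in the intervention arm.

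The article also discloses the turnover openly, which counts in its favour.

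**Conclusion.** The point holds in limited form. On either reading, 2 or 3 of the 12 final sites were not in the draw, 2 or 3 of the 6 pairs are broken, and at least one undrawn site is in the intervention arm. The description of sites randomised within pairs therefore does not fit the final 12, and the claim of unaffected score balance does not follow from the figures given. Neither direction nor size of bias can be established. About 0.38 points/month per entering site, and a net between −0.38 and +1.15, are illustrations that rest on the assumed one-SD advantage. Against a detectable difference of 6.1 this is modest: worth correcting, but not a fatal flaw.

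**What to change.** 1. **Report the turnover.** For each lost and entering site, give arm, pair, date and method of assignment. Resolve whether the third replacement had declined or had been randomised. Give survey means by arm for the final 12 sites.
2. **Qualify the randomised claim.** Describe any slot filled without a draw as not randomly allocated, and repeat the main contrast without those sites. State beforehand that an analysis of intact pairs has only 3 or 4 pairs, so a null result there says little.
3. **Define the intent-to-implement set from randomisation.** Where access to VA database records is approved, add a sensitivity analysis of the monitoring outcomes on the 12 sites first drawn, in their original arms. Phases are anchored to the intervention site's first visit, so a lost site has no dates of its own. Use those of the replacement in its slot or of its matched pair.

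The cost is a few extra model runs and possibly a data-access approval. Chart-based management outcomes would not be available for the withdrawn sites. Retrospective data were still being collected when the article was written (Trial status), so this can be done without changing the conduct of the trial.
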